## Abstract

**Background:**

Catheter ablation is routinely used to treat scar-related atrial tachycardia (s-AT). Conventional ablation often involves creating anatomical “lines” that transect myocardial tissue supporting reentry. This can be extensive, creating iatrogenic scar as a nidus for future reentry, and may account for arrhythmia recurrence. High-density mapping may identify “narrower isthmuses” requiring less ablation, with ripple mapping proven to be an effective approach in identifying. This trial explores whether ablation of narrower isthmuses in s-AT, defined using ripple mapping, results in greater freedom from arrhythmia recurrence compared to conventional ablation.

**Methods:**

The Ripple-AT-Plus trial (registration ClinicalTrials.gov, NCT03915691) is a prospective, multicentre, single-blinded, randomised controlled trial with 12-month follow-up. Two hundred s-AT patients will be randomised in a 1:1 fashion to either “ripple mapping-guided isthmus ablation” vs conventional ablation on the CARTO3 ConfiDENSE system (Biosense Webster). The primary outcome will compare recurrence of any atrial arrhythmia. Multicentre data will be analysed over a secure web-based cloud-storage and analysis software (CARTONET^TM^).

**Conclusion:**

This is the first trial that considers long-term patient outcomes post s-AT ablation, and whether targeting narrower isthmuses in the era of high density is optimal.

## Background

Scar-related atrial tachycardia (s-AT) can cause significant patient symptoms. These arrhythmias are often iatrogenic, secondary to scar created from prior atrial fibrillation (AF) ablation or cardiac surgery [1, 2]. As AF ablation is ever increasing, so too is the burden of these arrhythmias on healthcare systems [3, 4]. 3D mapping and catheter ablation is proven superior to anti-arrhythmic drugs in the treatment of these arrhythmias [5, 6]. However, arrhythmia recurrence remains a real issue for electrophysiologists.

S-AT ablation often involves creating “lines” that transect atrial tissue that support reentry. These lines are classified by their bordering anatomical structures (e.g. roof line, mitral line). Blocking conduction across these lines is important to prevent tachycardia recurrence. These lines can be significant in length, and achieving block can be challenging. Arrhythmia recurrence can occur secondary to “gaps” within these lines. Furthermore, if the delivery of ablation is excessive, this can cause iatrogenic scar and future reentry.

In the era of high-density mapping, “narrower isthmuses” supporting slow conduction bounded by scar are considered alternative ablation targets compared to linear anatomical based lesions. A comparison of outcomes between ablation targeting a narrow isthmus or anatomical linear lesions has yet to be performed; hence, operators may vary in their preferred ablation strategy. We hypothesise that an isthmus-targeted ablation of s-AT is superior to conventional ablation in reducing long-term recurrence, primarily as it may require less ablation with shorter procedural duration.

To test this hypothesis, we plan to identify narrow isthmuses using the “Ripple Map scar thresholding” technique, as we have shown this to be superior to conventional mapping in identifying narrow isthmuses (Ripple-AT Study) [7]. We look to compare outcomes of S-AT ablation targeting the narrowest identified isthmus with ripple mapping, with conventional mapping and ablation approaches (which often require linear lesions).

## Methods

### Study design

Ripple-AT Plus (ClinicalTrials.gov identifier number NCT03915691) is planned as a prospective, multicentre, single-blinded, randomised controlled superiority trial. The protocol was approved by the research ethics committee 19/LO/0637.

The target recruitment number is 200 with a 1:1 randomisation to either a “Ripple Map scar thresholding”-guided isthmus ablation or a “conventional mapping and ablation”. The primary end-point is documented ECG or Holter recurrence of any atrial arrhythmia which will be assessed at 3, 6, 9 and 12 months. All patients will undergo a 24-h Holter at 12 months.

### Randomisation

Randomisation will be done prior to the catheter ablation procedure. This will be done via a secure web interface with treatment allocation stratified by centre and controlled using a block system with random variation.

The study will be performed according to the study protocol, Good Clinical Practice as defined by the National Institute of Health Research (NIHR) and all applicable regulatory requirements.

### Ablation analysis

Anonymised mapping and ablation data will be analysed by the research team using a novel cloud-based storage and analysis software (CARTONET Microsoft Azure cloud, Biosense Webster) that securely transfers and uploads 3D mapping cases within the CARTO-3 system for remote review (https://eu.cartonet.net/login) via a Siemens teamplay gateway (Siemens, Malvern, PA).

### Eligibility criteria

Potentially eligible patients will be those referred for catheter ablation of AT by their direct care team, according to standard clinical guidelines. The investigators will identify potentially eligible patients for recruitment according to pre-defined inclusion and exclusion criteria.

### Inclusion

Referred for catheter ablation of s-AT (post-surgical*, post-ablation, idiopathic atypical atrial flutter**) by the direct clinical care team.Male or female, aged ≥ 18 years old.Able to consent for recruitment to the trial and the catheter ablation procedure.

*Post-surgical refers to cardiac surgery specifically and not CABG alone.

**Idiopathic atypical flutter includes any non-CTI flutter dependent upon constrained activation/slow conduction involving idiopathic scar to facilitate re-entry.

### Exclusion

Contraindication to catheter ablation as deemed by the clinical team.Typical atrial flutter or atrial fibrillation on ECG.

Patients not in stable AT for the duration of mapping, or those with non-inducible AT on the day of the procedure, will be excluded from the study.

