### Procedural setup

The peri-procedural anticoagulation regime is according to physician discretion but in line with established HRS/ESC guidelines, and TOE or CT may be used to exclude LA or LAA thrombus. General anaesthesia or sedation will be used as per local preference. 3D electroanatomical mapping will be performed using CARTO with the ConfiDENSE and ripple mapping modules (Biosense Webster Inc.). Once femoral vein access is established, a multi-polar electrode catheter will be inserted into the coronary sinus (CS) as a reference. The direction of activation on the CS catheter will be assessed. Following determination of the chamber of interest, high-density mapping of that chamber or both chambers is undertaken.

Intracardiac mapping will be performed in a stable AT using a multipolar catheter (Pentaray or Octaray) to cover the anatomy with colour threshold of 5. Standard ConfiDENCE filters will be applied to avoid erroneous point collection on the map. These include: (1) cycle length stability within 5% range; (2) electrode position stability within 2mm; (3) LAT stability filter at 3 milliseconds; (4) tissue proximity index to the endocardial surface.

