### Interventions

#### Arm 1

Ripple mapping displays acquired EGMs as a white oscillating bar which can be displayed over any base map. This property allows operators to view a Ripple Map over a bipolar voltage map on the same display. This allows the operator to identify areas of slow conduction in low-voltage regions. Cases will be commenced with bipolar scar thresholds of 0.5 mV. Operators will identify areas of Ripple activation, and the voltage settings will be sequentially reduced until a threshold is reached where no further Ripple Bar activation is seen. This scar thresholding method is shown in Fig. 1. The operators are then encouraged to identify the narrowest isthmus for ablation (Fig. 2). Entrainment is permitted after mapping if the operator feels it is necessary for the diagnosis.

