**Fig. 2 Fig2:**
[figure not shown]
Post AF ablation scar related Atrial Tachycardia (s-AT). (**A**) Ripple activation travels craniocaudal along the left atrial roof. The Ripple Scar Thresholding technique defines the scar threshold at 0.12mV. (**B**) A narrow isthmus bordered by scar is revealed on the anterior wall (activation time +50ms). (**C**) The two potential ablation strategies are a conventional roof line (1) or narrow isthmus ablation (2)

#### Arm 2

In the conventional mapping and ablation arm, all conventional CARTO activation mapping techniques (including LAT mapping, Extended Early Meets Late, Coherence) can be utilised as per operator preference. Entrainment is permitted after mapping if the operator feels it is necessary to make a diagnosis. Ripple mapping is not permitted. Once a diagnosis is made, the ablation set is planned as per operator preference.

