### Blinding

The patient, the local clinical team assessing the patient during the follow-up period and the research team assessing endpoints will all be blinded to which arm the patient was assigned to.

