### Sample size calculation

The sample size for this study is based on previous evidence published by our group. In a non-randomised, prospective study comparing ripple mapping–guided ablation to conventional mapping–guided ablation, the diagnostic accuracy was 90% and 65% respectively [10]. A similar effect size was also seen in a randomised prospective study (Ripple-AT Study), showing acute success was 90.5% and 70.7% respectively. In order to detect a difference between arms with 90% power and an alpha value of 0.05, at least 80 patients would be needed to be randomised to each treatment arm. Accounting for potential non-completion of protocol (10%) and loss to follow-up (10%), a minimum of 200 patients will need to be enrolled. Power calculations were performed using the G*Power software (University of Dusseldorf).

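### Patients are randomised before the procedure, then excluded during it for non-inducible or unstable AT by an operator who is not blinded, which puts the randomised comparison at risk of selection bias

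*Protocol article*

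**What the plan says.** All references are to the protocol article.

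- **Randomisation:** "Randomisation will be done prior to the catheter ablation procedure", by secure web interface and stratified by centre.
- **Exclusion:** "Patients not in stable AT for the duration of mapping, or those with non-inducible AT on the day of the procedure, will be excluded". The sentence goes on to say that the exclusion is from the study, so it is not confined to a per-protocol set.
- **Procedural setup:** "Intracardiac mapping will be performed in a stable AT using a multipolar catheter". This follows femoral access. One acquisition set-up is given for all patients, with the same choice of catheters, the same colour threshold and the same four filters.
- **Interventions:** in Arm 1, "the voltage settings will be sequentially reduced until a threshold is reached where no further Ripple Bar activation is seen". In Arm 2, "Ripple mapping is not permitted".
- **Blinding:** "The patient, the local clinical team assessing the patient during the follow-up period and the research team assessing endpoints will all be blinded". The operator is not listed.
- **Study endpoints:** recurrence is counted over the 12 months after ablation, with a 2-month blanking period.
- **Progress:** 33 patients had been randomised when the article was written, against a target of 200.

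**The concern.** A randomised patient can be excluded without bias if the criterion is judged in ignorance of the arm and the arm cannot affect it. The text does not secure this. The operator must know the allocation in order to follow it, and that same operator is in the lab when AT is induced and judged stable or not. The Exclusion section sets no threshold for stability. The 5% cycle-length figure in Procedural setup is a filter on point collection and not a rule for removing patients. How hard to try to induce AT, and when to call an AT unstable, is therefore left open to judgement with the arm known.

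If exclusions then differ between arms, in number or in the kind of patient removed, the remaining groups are no longer the groups that randomisation formed. A difference in 12-month recurrence could reflect who was removed and not what was done. Follow-up is counted from ablation and the rule removes the patient from the study, so an excluded patient may have no recorded outcome unless the protocol asks for one. The Limitations section does not mention this.

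**Working it through.** **Step 1: order of events.** Allocation comes before the procedure (Randomisation). Induction and mapping take place within the procedure (Exclusion, Procedural setup). The operator is not listed as blinded (Blinding). The exclusion is therefore made after allocation and with the arm known. No arithmetic is needed for this part.

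**Step 2: the plan's own figure.** Sample size calculation gives 80 per arm and 200 in total. With 90.5% against 70.7%, two-sided alpha 0.05 and 90% power, the pooled formula gives 82 per arm and the arcsine formula 79. Inflation is 160 / (1 − 0.20) = 200. The figure is reproduced. The point here does not depend on it, except that 200 gives 100 randomised per arm.

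**Step 3: what unequal exclusion could do.**

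*Inputs.* From the documents: 100 randomised per arm, and 25% recurrence at 12 months (quoted in the Discussion for the earlier study). Assumed: no true effect, exclusion fractions e of 5% and 15%, and a recurrence risk r among excluded patients. The documents give neither e nor r.

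*Formulas.*
- Observed recurrence among those kept: (0.25 − e·r) / (1 − e).
- Standard error of the difference: √[p(1 − p)(1/95 + 1/85)], where p is the pooled observed rate.
- With z = difference / SE, two-sided type I error = 1 − Φ(1.96 − z) + Φ(−1.96 − z).

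*Worked case, r = 50%.*
- 5% excluded: (0.25 − 0.025)/0.95 = 23.7%.
- 15% excluded: (0.25 − 0.075)/0.85 = 20.6%.
- Difference 3.1 points; p = 0.40/1.80 = 0.222; SE = 0.0621; z = 0.50; type I error 7.9%.

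| Recurrence in excluded (r) | Kept, 5% excluded | Kept, 15% excluded | Spurious difference | Type I error |
|---|---|---|---|---|
| 10% | 25.8% | 27.6% | −1.9 points | 5.9% |
| 25% | 25.0% | 25.0% | 0 | 5.0% |
| 35% | 24.5% | 23.2% | 1.2 points | 5.4% |
| 50% | 23.7% | 20.6% | 3.1 points | 7.9% |
| 60% | 23.2% | 18.8% | 4.3 points | 11.0% |

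A positive difference favours the arm with more exclusions. Other imbalances at r = 50%:
- 5% against 10% excluded: 1.5 points and 5.6%.
- 5% against 20% excluded: 4.9 points and about 12%.

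Starting from 80 followed per arm instead of 100, the 50% and 60% rows become 7.3% and 9.8%.

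**Step 4: equal numbers, different patients.** Exclude 10% in each arm, with r = 50% in one arm and 25% in the other. The kept rates are (0.25 − 0.05)/0.90 = 22.2% and (0.25 − 0.025)/0.90 = 25.0%, a spurious 2.8 points. If number and risk are both equal, the difference is zero and type I error stays at 5%.

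**The case against.** **The technique itself is not shown to drive exclusion.** A reader might infer that mapping lasts longer in one arm, so that AT has more time to become unstable there. The documents do not support that. Procedural setup gives one acquisition set-up for everyone, and Arm 1 describes ripple mapping as a way of displaying electrograms already acquired. Non-inducibility comes before any arm-specific step. This objection stands, and it narrows the concern to judgement exercised with the allocation known.

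**The size of the bias is assumed.** This also stands. The larger figures need both a clear imbalance and excluded patients whose risk is well above average. The documents do not show that such patients recur more, and non-inducible patients might recur less. In addition, a circuit that changes after ablation is not an exclusion, because the Ablation section keeps that patient under the allocated arm.

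**An analysis-population statement may exist elsewhere.** The workflow figure is not shown and the article condenses a fuller protocol. The point does not rest on a missing intention-to-treat statement. It rests on the stated rule that these patients leave the study. A statement elsewhere that all randomised patients are analysed would have to be reconciled with that rule.

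**Two further readings go too far.**
- One is that the allowance in Sample size calculation ("Accounting for potential non-completion of protocol (10%) and loss to follow-up (10%), a minimum of 200 patients will need to be enrolled") costs power because non-completers should be counted as dilution. That assumes an analysis population the text does not name, and it equates non-completion with the Exclusion rule, which the text does not do.
- The other is that the bias could never be repaired. Excluded patients can be followed, and the endpoint draws on ECGs and Holters from routine care as well as the study Holter at 12 months.

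**Conclusion.** The concern holds as a risk to the randomised comparison that the stated rules create. It does not show that the comparison is already broken. The order of events and the absence of the operator from the blinded list are plain in the text. Whether bias follows depends on exclusions differing by arm, on which the documents give no figures, so its size and direction are unknown.

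Under the illustrative 5% against 15% exclusion, type I error runs from 5.0% (excluded patients at average risk) to about 8% and 11% (recurrence of 50% and 60%). The sign reverses below average risk. These figures rest on assumed exclusion fractions and risks, and they show what is possible, not what is expected. The point still merits a change to the protocol, because the remedy is cheap and, at the time of writing, 200 − 33 = 167 of the planned patients had yet to be randomised.

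**What to change.** **For future patients:** randomise in the lab, through the existing web interface, once stable AT is confirmed and the map has been acquired. Acquisition is set up in the same way for both arms, so allocation is needed only for displaying and reading the map and for planning ablation. Reword the Exclusion section so that non-inducible or unstable AT excludes a patient only before randomisation.

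**For patients already randomised, and for any later exclusion after randomisation:** follow them for 12 months, keep them in the primary analysis in the arm to which they were randomised, and report exclusions by arm and reason. Since the endpoint clock now starts at ablation, state from which date it runs for these patients; the date of randomisation is the natural choice. Use the stable-AT set as a sensitivity analysis.

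**Cost:** a protocol amendment, a log-in during the case, and follow-up of patients who would otherwise have been excluded. If randomising in the lab proves impractical at some centres, applying the second paragraph to everyone randomised is the minimum. It protects the comparison without changing the timing of allocation.

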### Procedural setup

The peri-procedural anticoagulation regime is according to physician discretion but in line with established HRS/ESC guidelines, and TOE or CT may be used to exclude LA or LAA thrombus. General anaesthesia or sedation will be used as per local preference. 3D electroanatomical mapping will be performed using CARTO with the ConfiDENSE and ripple mapping modules (Biosense Webster Inc.). Once femoral vein access is established, a multi-polar electrode catheter will be inserted into the coronary sinus (CS) as a reference. The direction of activation on the CS catheter will be assessed. Following determination of the chamber of interest, high-density mapping of that chamber or both chambers is undertaken.

Intracardiac mapping will be performed in a stable AT using a multipolar catheter (Pentaray or Octaray) to cover the anatomy with colour threshold of 5. Standard ConfiDENCE filters will be applied to avoid erroneous point collection on the map. These include: (1) cycle length stability within 5% range; (2) electrode position stability within 2mm; (3) LAT stability filter at 3 milliseconds; (4) tissue proximity index to the endocardial surface.

### Interventions

#### Arm 1

Ripple mapping displays acquired EGMs as a white oscillating bar which can be displayed over any base map. This property allows operators to view a Ripple Map over a bipolar voltage map on the same display. This allows the operator to identify areas of slow conduction in low-voltage regions. Cases will be commenced with bipolar scar thresholds of 0.5 mV. Operators will identify areas of Ripple activation, and the voltage settings will be sequentially reduced until a threshold is reached where no further Ripple Bar activation is seen. This scar thresholding method is shown in Fig. 1. The operators are then encouraged to identify the narrowest isthmus for ablation (Fig. 2). Entrainment is permitted after mapping if the operator feels it is necessary for the diagnosis.

**Fig. 1 Fig1:**
[figure not shown]
Ripple Map scar thresholding technique. **A** The Ripple Map of this s-AT circuit is played on a bipolar voltage map set at 0.50–0.50 mV. Ripple Bars are seen in the tissue coloured red (< 0.50mV). **B** The voltage limits are reduced sequentially to 0.30–0.30mV. Ripple Bars can still be seen in the tissue coloured red. **C** The voltage limits are further reduced until no Ripple Bars are seen in the tissue coloured red. This defines the scar threshold at 0.12 mV

**Fig. 2 Fig2:**
[figure not shown]
Post AF ablation scar related Atrial Tachycardia (s-AT). (**A**) Ripple activation travels craniocaudal along the left atrial roof. The Ripple Scar Thresholding technique defines the scar threshold at 0.12mV. (**B**) A narrow isthmus bordered by scar is revealed on the anterior wall (activation time +50ms). (**C**) The two potential ablation strategies are a conventional roof line (1) or narrow isthmus ablation (2)

#### Arm 2

In the conventional mapping and ablation arm, all conventional CARTO activation mapping techniques (including LAT mapping, Extended Early Meets Late, Coherence) can be utilised as per operator preference. Entrainment is permitted after mapping if the operator feels it is necessary to make a diagnosis. Ripple mapping is not permitted. Once a diagnosis is made, the ablation set is planned as per operator preference.

### Ablation

Radiofrequency ablation is delivered by the SmartTouch ThermoCool Catheter/Q-Dot catheter and its appropriate generator (Biosense Webster Inc.). Power and duration of radiofrequency energy delivered will be standardised using modified CLOSE protocol [8]. Each ablation lesion will be delivered using an inter-lesion distance of < 6 mm targeting an ablation index no greater than 400 on the posterior wall and 550 on the anterior wall or an impedance drop of 10 ohms. Standardising ablation delivery allows data collection regarding overall ablation by counting the number of lesions and also the length of the ablation lesions.

If the tachycardia circuit changes after ablation, then the protocol above as per the allocated arm is followed. If ablation is unsuccessful (defined by no restoration of sinus rhythm), then further mapping (as per the allocated arm) and ablation is permitted. Once sinus rhythm has been restored, all ablation sets including prior lesions (e.g. previous PVI) are checked using the allocated mapping technique to ensure they are still blocked with further ablation permitted if reconnected. In those with a documented history of AF, a de novo bilateral WACA is permitted at this stage if not already done as part of planned lesion set. If sinus rhythm is not restored at the end of the case, patients undergo DCCV to sinus rhythm. The use of AAD’s is documented throughout the study. Clinicians are permitted to adjust the AAD therapy as appropriate. The study does not seek to influence this practice.

